### Safety

2.5

The 25(OH)D used in this trial already exists in the market, which has safety and quality. It was decided to 2 doses of vitamin D: 14,000 IU and 28,000 IU per week. The first one corresponds to maintenance therapy (1500 to 2000 IU per day) for replacement adult population at risk for hypovitaminosis D, in accordance with the Brazilian Society of Endocrinology and Metabolism^[1]^ and Endocrine Society.^[3]^ The second is double of maintenance therapy. It was decided to use this low dose to verify if the maintenance therapy is able to reduce hypertriglyceridemia, and double dose in order to increase the probability of generating a significant difference in the vitamin D status between the treatment groups and placebo. The clinical trial lasts for 12 months due to the seasonality of the incidence of ultraviolet radiation.^[21]^ In addition, vitamin D has endogenous synthesis via exposure to the sun and can be stored in adipose tissue,^[3]^ factors that make the placebo group necessary.

The risk of intoxication should be considered, but this condition is rare and caused by the intake of extremely high doses of vitamin D for long periods. The clinical symptoms of intoxication are characterized by hypercalcemia, hyperphosphatemia, suppression of PTH levels which can lead to nephrocalcinosis, and soft tissues calcification, especially blood vessels, in addition to fatigue, weight loss, anorexia, and impairment of renal function.^[1,3]^ The safe value of serum vitamin D levels suggested to avoid hypercalcemia is less than 150 ng/mL.^[3]^

Safety evidence for 25(OH)D supplementation has been reported by the Endocrine Society^[3]^ and by others authors, who did not observe serious adverse events. In a randomized trial, vitamin D supplementation with 6000 IU daily for 3 months, after 3000 IU daily for more 3 months and 2200 IU daily for more 3 months, was not associated with any adverse events or hypercalcemia during all 9 months of the study.^[22]^ In the vitamin D, diet and activity study, 2000 IU of cholecalciferol daily were supplemented for 12 months, and 4 women reported light-headedness, severe headaches, nausea, rash/hives, weakness/numbness, and constipation.^[17]^

Symptoms of vitamin D intoxication include dizziness, headache, nausea, rash, urticaria, weakness, numbness and constipation, hypercalcemia, hypercalciuria, and associated kidney stones. To minimize the risk of vitamin D supplementation, individuals with a diagnosis of renal, hepatic, or thyroid disease were excluded. As a safety precaution, participants with 25(OH)D >50 ng/mL (or 159 nmol/L) associated with altered serum calcium levels (>11 mg/dL) and confirmation of a second test with altered serum calcium (>11 mg/dL) and PTH (<10 pg/mL) levels or evidence of vitamin D intoxication symptoms (dizziness, headache, nausea, rash, urticaria, weakness, numbness, and constipation) are excluded from trial. Additionally, measures will be taken to record adverse events or reactions: by the follow-up questionnaire every 4 months or in spontaneously by the participant by telephone/message or email to the responsible team.

### Sample size

2.6

The sample was calculated with the following assumptions: the percentage of hypertriglyceridemia in the group not exposed to vitamin D replacement (40%)^[23]^; the percentage of hypertriglyceridemia in the group exposed to vitamin D replacement (22%)^[11]^; and the likelihood ratio equal to 2.3^[11]^, considering 80% power and a 95% confidence level. As a result, this study requires 106 participants in each group; after adding 10% for losses, a total of 350 participants at least were enrolled. To estimate the sample size, OpenEpi software (Open Source Epidemiologic Statistics for Public Health, EUA) version 3.01, a web-based epidemiologic and statistical calculator for public health, was used.

### Recruitment

2.7

All rotating shift workers from 5 units of an iron ore mining company are invited by study researcher to participate in screening for a general health assessment. The screening visit is used to identify eligible participants. After identifying the potential participant, the study investigator invites the individual to participate in the clinical trial. The invitation is made for individual or group face-to-face interviews, to clarify any doubts, to sign the consent form and to delivery to the participant a copy of the consent form.

### Randomization

2.8

Randomization will be used to ensure a balance between the 2 intervention groups and placebo group for deficient and insufficient vitamin D frequencies. The groups were also balanced by the following cardiovascular risk factors: fasting glucose, HDL cholesterol, triglycerides, LDL cholesterol, blood pressure, and waist circumference (Table 1).

**Table 1 T1:**
[figure not shown]
Criteria for allocating participants: parameters and their categories.

The allocation of the individuals were performed by an algorithm developed in R software version 3.5.1 [R Development Core Team (2018), R Foundation for Statistical Computing, Vienna, Austria] language that guarantees the similarity of the groups in relation to the total sample (eligible) considering a final sample (selected) weighted by the parameters and categories considered (Table 1). This method allocates the individuals with the greatest similarity between the frequencies of the categories of each parameter of the total sample among the subgroups of the clinical trial,^[24]^ similar to propensity score matching.^[25]^ The steps used in the allocation process of the patients in the groups of this clinical trial are presented below, considering a sample of *p* variables with a total of *m* categories:

First step: Initially, the algorithm performs the data reading, registers the number of categories present in each variable, and stores them in an ordered vector;

Second step: The algorithm receives the proportions of the categories of each variable and creates an ordered vector containing the proportions of the categories of each variable of the complete original sample *Pobs* *=* (*p*_1_, *p*_2_…, *p*_3_);

Third step: It randomly divides the initial sample into *k* groups of equal size *n*/*k*, where *n* is the sample size. If the result obtained from *n*/*k* is not an integer algorithm, the size of each group will be rounded to the next integer. Thus, the number of elements in the groups is defined;

Fourth step: After dividing the *k* groups, the proportions of the categories of each variable and each of the groups are calculated according to 1st and 2nd steps and the proportions vector *P*_1*k*_ = (*P*_2*k*_,*…, P*_*mk*_);

Fifth step: Sum of the Euclidean distances between the vectors of proportions of the *k* subsamples and the original proportions of the total sample, is defined as *D*_0_. That is: 

This will be the metric used in the simulation.

Sixth step: New subsamples are generated according to 4th step and a new metric is calculated for the new subsamples according to 6th step, namely: 

Seventh step: The subsample metrics are compared. The sample whose subgroup division presents the lowest value of *D* is maintained as the most probable sample to the original and will be the basis of the next simulation. The sample with the highest value of *D* will be discarded.

Eighth step: Repeat 6th–7th steps until the metric *D* reaches a predetermined stopping criterion or until a certain maximum number of simulations occurs. The sample with the lowest *D* value will be the one with the highest similarity in terms of the proportion of the categorical variables between the groups when compared to the original proportions.^[24]^

## Blinding

3

Double-blind masking was maintained for the participants and the team members in direct contact with the participants. Only 1 researcher in the Laboratory of Cardiometabolism, School of Medicine of the Federal University of Ouro Preto, who is not involved in the data collection, has the knowledge of this information. This researcher was responsible for allocating the participants to the intervention or placebo groups and for receiving the packaged and encapsulated supplements.

### Data collection

3.1

The screening was performed in a population of 686 rotating shift workers; all individuals were invited to a general health assessment. All data were collected at the company's clinic through face-to-face interviews with a structured questionnaire assessment and a blood draw. The team responsible was composed of nurses, biochemists, nutritionists, and students, who were trained to collect the data before the study.

Figure 1 demonstrates all measurements that were evaluated at the screening visit, follow-up visits, and at the end of the 12-month supplementation period. At the screening visit, we are evaluating socioeconomic status, pre-existing diseases, drug use, sun exposure, lifestyle profile, quality of life, cognition (Table 2), blood pressure, biochemical data (Table 3), and anthropometrics and body composition measurements (Table 4). The follow-up visits will occur every 4 months and the supplementation delivery will occur every 2 months (it was integrated with follow-up visits). The follow-up visit procedures include blood sample collection, waist circumference measurement, and questionnaire interview. The vitamin D and lipid profile levels were quantified. The follow-up questionnaire monitors a presence of vitamin D intoxication, disease symptoms, drugs use, vitamins and minerals supplements, disease presence, treatment and others interventions during the trial, and food consumption alteration. At the end of the 12-month supplementation period, a reassessment of the general state of health was performed (Fig. 1).

**Figure 1 F1:**
[figure not shown]
Clinical trial procedures schedule.

**Table 2 T2:**
[figure not shown]
Components of interviews.

**Table 3 T3:**
[figure not shown]
Biochemical analyses and blood pressure examinations and measurements.

**Table 4 T4:**
[figure not shown]
Anthropometry examinations and measurements.

The blood samples were collected after 10 hours of fasting by nurse and pharmacist of responsible team. Every follow-up visit the blood samples are analyzed immediately on fresh samples, and aliquots are stored frozen at −80°C. The procedures and biochemical analyses were performed by pharmacist of responsible team at the Laboratory of Pilot and Clinical Analyses (LAPAC/UFOP) and Laboratory of Epidemiology of Parasitic Diseases of the Federal University of Ouro Preto School of Medicine (Table 3).

Body composition was measured using the portable segmental tetrameric bioimpedance monitor Tanita model BC558 (Tanita Corporation of America Inc, Arlington Heights, IL). The following data were collected: body fat percentage (total and segmental), visceral body fat, skeletal muscle mass (total and segmental), total body water, total bone tissue, and basal metabolic rate. For the measuring process, the participant were standing barefoot in the platform center, without wearing or holding any heavy objects, looking straight ahead,^[27]^ with their feet placed on the 2 lower electrodes while holding the 2 upper electrodes with their arms extended away from the trunk, and without moving or talking during measurement. Four hours of fasting, an empty bladder, minimal dress, absence of heavy metal, and no strenuous exercise was also required before measurement, according to the Tanita manual (Table 4).

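### A pharmacist with direct participant contact also runs the 25(OH)D assay during follow-up, so the claimed masking of contact staff is not fully protected

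*Protocol article*

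**What the plan says.** On masking, the Blinding section states: "Double-blind masking was maintained for the participants and the team members in direct contact with the participants". It adds that one researcher, "who is not involved in the data collection, has the knowledge of this information".

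On who handles the blood, section 3.1 (text after Table 4) states: "The blood samples were collected after 10 hours of fasting by nurse and pharmacist of responsible team". A little later it states: "The procedures and biochemical analyses were performed by pharmacist of responsible team".

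On timing and content, section 3.1 says: "The follow-up visits will occur every 4 months"; "Every follow-up visit the blood samples are analyzed immediately on fresh samples"; and "The vitamin D and lipid profile levels were quantified". Waist measurement and a questionnaire interview take place at the same visits. General health is reassessed at 12 months.

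On use of the result, section 2.2 includes a 25(OH)D threshold, combined with serum calcium, among the criteria applied after each visit for interrupting follow-up.

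On why 25(OH)D relates to the arm, section 2.5 explains that the double dose was chosen "to increase the probability of generating a significant difference in the vitamin D status between the treatment groups and placebo". The lower dose has a different reason: to see whether a maintenance-level dose reduces hypertriglyceridemia.

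**The concern.** Double-blinding can fail without anyone opening the code, if staff who deal with participants see a laboratory value that the treatment is meant to move. In this trial that value is 25(OH)D. The article gives one role both the contact with participants and the assay, and the results exist while later outcomes are still to be collected.

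The measures at stake are those that depend on an observer:

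- waist circumference and cognition, both secondary outcomes in section 2.4;
- symptom recording, which under section 2.2 can end follow-up;
- compliance, ascertained by interview and message (section 2.3). Non-compliance with the protocol is the ground for exclusion from the per-protocol population (section 3.2).

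**Working it through.** The plan gives no figure for this point, so the check has two parts: a comparison of the statements, and an illustration on assumed values.

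**Comparison of the statements**

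1. Masked group (Blinding): participants and team members in direct contact with them.
2. Direct contact (3.1): drawing blood is direct contact, and a nurse and a pharmacist of the responsible team do it.
3. Assay (3.1): a pharmacist of the same team performs the analyses.
4. Timing (3.1): analysis is immediate at each follow-up visit, not batched at the end. With visits every 4 months, results from months 4 and 8 exist before the 12-month reassessment.
5. Analyte (3.1): vitamin D is quantified at follow-up.
6. Use (2.2): a 25(OH)D criterion is applied after each visit, so somebody reads the values during the trial.
7. Safeguards stated: a numeric identifier per participant and restricted links to stored data (3.4), lipid results named as those returned to participants (2.3), and code breaking only by the code keeper (2.2). None of these masks the assayer or withholds 25(OH)D from contact staff.

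Steps 2 to 6 place a value related to allocation in the hands of a role that step 1 says is masked.

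**How much one 25(OH)D value could reveal**

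Inputs: the article gives neither the expected active-placebo difference *d* nor the within-arm SD. Both are assumed here: *d* from 6 to 15 ng/mL and SD from 6 to 8 ng/mL. The two active arms are treated as one normal distribution with the same SD as placebo.

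Formula: with a cut-off midway between the means, the proportion classified correctly in each group is Φ(*d* / (2·SD)).

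| *d* (ng/mL) | SD (ng/mL) | *d*/(2·SD) | Correct |
|---|---|---|---|
| 6 | 8 | 0.375 | 65% |
| 6 | 6 | 0.500 | 69% |
| 10 | 8 | 0.625 | 73% |
| 10 | 6 | 0.833 | 80% |
| 15 | 8 | 0.938 | 83% |
| 15 | 6 | 1.250 | 89% |

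A wider range (*d* 5 to 20, SD 6 to 10) gives 60% to 95%.

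**Benchmark**

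These are balanced accuracies, for which no information means 50%. Under 1:1:1 allocation two thirds of participants are on active treatment. Guessing active for everyone is therefore right for 2/3 = 67% overall, but wrong for every placebo participant, so its balanced accuracy is (100% + 0%)/2 = 50%. The midpoint rule has the same accuracy in both groups, so its overall proportion correct is also 65% to 89%. Against the 67% yardstick this runs from 65 − 67 = −2 points to 89 − 67 = +22 points. At the small end the midpoint rule gains nothing in overall hits, although it does identify some placebo participants. At the large end the gain is substantial.

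**The case against.** The strongest reply is that the overlap concerns one role, not the field team. Section 3.1 describes a mixed team of nurses, biochemists, nutritionists and students. Nowhere does it say that the pharmacist measures waist, tests cognition or judges compliance. The text names a role, so different people could draw and assay. Tables 2 to 4 and Figure 1, which may give more detail, are not shown. This stands: bias in those measures is conditional on the pharmacist taking part or passing values on.

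A second reply is that tube coding and result routing are details an article leaves to its full protocol. Had the article merely been silent on them, there would be no point to make. But it states who is masked, who draws, who assays and when, and those statements do not fit together without a barrier that it does not describe.

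A reader might infer that 25(OH)D is close to an allocation label, or that the blind was in fact broken. The documents support neither. Section 2.5 ties only the double dose to a difference in vitamin D status, and a group difference is not an individual label. The same section names seasonality and synthesis from sun exposure, which blur individual values. Staff would not know the midpoint used in the illustration, and the two active doses are harder to tell apart from each other than from placebo.

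Finally, the primary outcome and LDL are laboratory values, and an intention-to-treat analysis is planned beside the per-protocol one. This also stands and limits the reach of the point. One indirect route to the primary analysis remains: the intention-to-treat population is restricted to participants with outcome data, so symptom recording that ends follow-up could affect who is analysed.

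**Conclusion.** The point holds as a documented overlap in one role. The Blinding section claims masking for staff in direct contact. Section 3.1 gives a pharmacist of that team both the blood draw and the assays, including 25(OH)D, with results available during follow-up, and no stated step separates the two.

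The size is uncertain. A 25(OH)D value carries partial information on active versus placebo: 65% to 89% balanced accuracy under the assumed differences and SDs, against 50% for no information and beside a 67% overall hit rate from always guessing active. No figure in the article narrows this range.

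The consequence is a possible, not a demonstrated, bias in waist, cognition, symptom recording and compliance, and through compliance in the per-protocol set. It requires that the pharmacist assesses these or shares values with those who do. The primary triglyceride outcome is little affected. The matter is worth correcting because the protection is cheap, but it does not undermine the main comparison.

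**What to change.** Reconcile the Blinding section with section 3.1, as follows.

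- Relabel tubes with a laboratory code, so that the assay is run without participant identity.
- During follow-up, send individual 25(OH)D results only to a person without participant contact, outcome assessment or the allocation list. A designated data monitoring committee member who does not hold the code is one option. The existing code keeper is not suitable, because someone who knows the allocation would then help to decide whose follow-up ends.
- That person applies the existing section 2.2 criteria unchanged; only the reporting route moves.
- Release 25(OH)D to the trial team after database lock.

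The trial enrolled in November 2016 and was reported as not concluded, so some visits have probably taken place under the present arrangement. For those, report who saw 25(OH)D and when, and who measured waist, tested cognition and judged compliance. Qualify the double-blind claim for the waist, cognition and per-protocol results accordingly.

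The cost is a relabelling step and a changed reporting route, with field staff not seeing 25(OH)D during follow-up. Contacting the clinic when the criteria are met may still hint at active treatment, but only for the participants concerned.

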### Statistical methods

3.2

Baseline characteristics and follow-up measurements of the study population will be summarized separately within each group. The baseline characteristics are vitamin D, fasting glucose, HDL cholesterol, triglycerides, LDL cholesterol, blood pressure systolic, waist circumference, cognition, sex, age, race, calcium, PTH, albumin, creatinine, total cholesterol, sun exposure, alcohol, physical activity, and food consumption. The follow-up measurements will be demonstrated as continuous variables, which are vitamin D, HDL cholesterol, triglycerides, LDL cholesterol, waist circumference, and total cholesterol. For continuous variables, the means and standard deviations or medians, 25th and 75th percentiles will be presented. The ANOVA or the Kruskal–Wallis test will be use for continuous variables after evaluating normality and the equality of variances using the Kolmogorov–Smirnov and Levene tests, respectively. For categorical variables, the number and percentage of participants within each category will be presented. The Pearson chi-squared test or Fisher exact test will be used. For each variable (continuous or categorical), the percentage of missing values will be reported. For all tests, a *P* < .05 will be considered significant.

The analysis of primary and secondary outcomes will use an intention-to-treat (ITT) population and a per-protocol (PP) population. ITT population includes all participants for whom outcome data are available, in the group to which they were randomized, regardless of the treatment actually received. PP population excludes individuals who did not comply with the protocol. The primary and secondary outcomes, which are hypertriglyceridemia, high LDL cholesterol, waist circumference, and low cognitive impairment, will be compared separately between each treatment group and placebo, using binary logistic regression or regressão de Poisson, if the outcome is rare, 5% or less, and the relative risk (RR) is less than about 2^[47]^ for proportions (for binary outcomes), and using linear regression for differences in means (for continuous endpoints), with 95% confidence interval (CI). An analysis will be performed to check whether adjusting for age, duration of shift work, physical activity level, alcohol consumption, lower cholesterol drugs, and foods consumption (fiber, total carbohydrates, total fat, and saturated fat) has any impact on the estimated treatment effects; if it has no impact, then they will not be included in the model. Statistical analyses will be calculated using PASW (Predictive Analytics Software, SPSS Inc, Chicago, IL) version 17.0 and R software (R Development Core Team) version 3.5.1.

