### Participants

2.2

The study participants consisted of rotating shift workers from 5 units of a Brazilian iron ore mining company; all were adults aged between 18 and 60 years. The company's rotating shift schedule is 6 hours of work, followed by 12 hours of rest. All participants work 4 shifts on the following schedule: 7 PM to 1 AM, 1 PM to 7 PM, 7 AM to 1 PM, and 1 AM to 7 AM. After completing the 4-shift weekly cycle, they have a day off. The interviews and blood sample collection will occur in the workplaces.

The inclusion criteria are as follows:

25(OH)D levels <30 ng/mL (75 nmol/L)^[1]^With at least 1 of these parameters:Fasting glucose ≥100 mg/dL (5.55 mmol/L)^[19]^; HDL cholesterol <50 mg/dL (1.29 mmol/L) for women and <40 mg/dL (1.04 mmol/L) for men^[19]^;Triglycerides ≥150 mg/dL (3.88 mmol/L)^[19]^;LDL cholesterol ≥130 mg/dL (3.36 mmol/L)^[20]^;Blood pressure systolic ≥130 mm Hg or diastolic ≥85 mm Hg^[19]^;Waist circumference ≥80 cm for women and ≥90 cm for men.^[19]^

Subjects are excluded with evidence as following: malabsorption syndrome, kidney, liver, or thyroid diseases; specific drug use (anticonvulsants, corticosteroids, hormones, or vitamin and mineral supplements); or altered levels of serum creatinine, parathyroid hormone (PTH), serum calcium, or albumin. Among women, current breast feeding or pregnancy are also considered exclusion criteria.

After each visit (every 4 months), the follow-up will be interrupted if subjects evidence 25(OH)D >50 ng/mL (or 159 nmol/L) associated with altered serum calcium levels (>11 mg/dL) and with confirmation of a second test with altered serum calcium (>11 mg/dL) and PTH (<10 pg/mL) levels or evidence of vitamin D intoxication symptoms (dizziness, headache, nausea, rash, urticaria, weakness, numbness, and constipation); recent diagnosis of malabsorption syndrome, kidney, liver, or thyroid diseases; specific drug use (anticonvulsants, corticosteroids, hormones, or vitamin and mineral supplements); or participant request. In cases of interrupted due to intoxication, the code will be broken to clarify the diagnosis, only by the code keeper.

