### Outcome measures

2.4

The primary outcome to be evaluated is an 18% reduction in hypertriglyceridemia (≥150 mg/dL) between the pre and postintervention measurements. The secondary outcomes to be evaluated are a 36% reduction in hypertriglyceridemia (≥150 mg/dL) between the pre and postintervention measurements with 28,000 IU of vitamin D; an 18% reduction in high LDL cholesterol (≥130 mg/dL) between the pre and postintervention measurements; an 18% reduction in waist circumference (≥90 cm men; ≥80 cm women) between the pre and postintervention measurements; and a reduction in low cognitive impairment (by cognition tests) between the pre and postintervention measurements.

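### The population labelled ITT is an available-case set, and the stopping rules end follow-up as well as the supplement, so some randomised participants leave the primary comparison

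*Protocol article*

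**What the plan says.** **Analysis set.** In the protocol article, Statistical methods, the "ITT population includes all participants for whom outcome data are available", analysed "in the group to which they were randomized, regardless of the treatment actually received". A separate per-protocol set leaves out those who did not comply. On missing values, the section commits only to reporting their percentage.

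**Stopping rules.** The Participants section states: "After each visit (every 4 months), the follow-up will be interrupted if subjects evidence" one of the listed conditions. These are:
- 25(OH)D above 50 ng/mL with serum calcium above 11 mg/dL, confirmed by a second test showing calcium above 11 mg/dL and PTH below 10 pg/mL;
- intoxication symptoms;
- newly diagnosed malabsorption, kidney, liver or thyroid disease;
- "specific drug use (anticonvulsants, corticosteroids, hormones, or vitamin and mineral supplements); or participant request".

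The Safety section says that people who meet the biochemical or symptom rule "are excluded from trial".

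**Primary outcome.** The Outcome measures section states: "The primary outcome to be evaluated is an 18% reduction in hypertriglyceridemia (≥150 mg/dL) between the pre and postintervention measurements". A participant therefore needs a measurement after the intervention to contribute.

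**The concern.** An ITT comparison is protected because everyone randomised is counted in the assigned group, whatever happens afterwards. Here two stated rules work against that. The first ends follow-up after certain post-randomisation events, and the second admits to the ITT set only those with outcome data. Nothing in the article says that interrupted participants are still measured at 12 months.

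The result sits badly with the promise to analyse people regardless of treatment received. Someone who starts a vitamin supplement is the kind of departure that an ITT set should keep. Under these rules that person loses follow-up and would usually be missing from both the ITT and the per-protocol sets, which brings the two analyses closer together.

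The losses need not be random. The 25(OH)D, calcium and PTH rule may relate to arm, because two of the three arms receive vitamin D. Thyroid, liver and kidney disease, corticosteroids and hormones may relate to lipids. Participants also receive their lipid results every 4 months (Interventions), so a request to leave can follow knowledge of the outcome. At stake are the credibility of the primary comparison and an ITT label that the set does not earn.

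**Working it through.** **1. The plan's own figures.** The Sample size section gives 40% hypertriglyceridemia without and 22% with vitamin D, 80% power, 95% confidence, 106 per group, 10% for losses, and 350 in total. With the pooled rate p = 0.31 and two-sided alpha 0.05:

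n = (1.960 + 0.842)² × 2 × 0.31 × 0.69 / 0.18² = 103.6, so 104 per group.

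This is close to the stated 106. The total is 3 × 106 = 318, and 318 × 1.10 = 349.8, so 350. These figures are not in dispute. The 10% is the only loss rate in the article. It covers losses of every kind and is not split by arm or cause.

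**2. The rules side by side.** A trigger is met at a 4-monthly visit, follow-up is interrupted, there is normally no postintervention triglyceride and hence no outcome data, and the participant is not in the ITT set. Every link except the missing final measurement is stated. That one is the natural reading of interrupted follow-up.

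**3. Illustrative bias with no true effect.** Assume 40% in both arms, a fraction L lost from one active arm only, and a rate q of hypertriglyceridemia among the lost. Then:

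observed active rate = (0.40 − L·q) / (1 − L)

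false benefit = 0.40 − observed rate = L·(q − 0.40) / (1 − L)

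| L | q | Observed active rate | False benefit (points) |
|---|---|---|---|
| 5% | 40% | 0.400 | 0 |
| 5% | 60% | 0.370/0.95 = 0.389 | 1.1 |
| 5% | 100% | 0.350/0.95 = 0.368 | 3.2 |
| 10% | 40% | 0.400 | 0 |
| 10% | 60% | 0.340/0.90 = 0.378 | 2.2 |
| 10% | 100% | 0.300/0.90 = 0.333 | 6.7 |

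If q is below 40%, the sign reverses and the treatment looks worse than it is. L and q are assumptions, since the article gives neither.

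**4. Generic outer bounds.** Take 40% v 22% among those observed and 10% lost in each arm.
- All lost active participants hypertriglyceridemic, no lost placebo participant so: 0.9 × 0.40 − (0.9 × 0.22 + 0.10) = 0.360 − 0.298 = 6.2 points.
- The reverse: (0.360 + 0.10) − 0.198 = 26.2 points.

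With whole participants at about 120 per arm (362/3), the observed 24/108 v 43/108 gives 5.8 to 25.8 points. The same bounds apply to any trial that loses 10% per arm, so they do not measure this flaw.

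**The case against.** Several stronger readings are tempting, and the article does not support them.

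- **That the ITT set holds completers only.** It does not. Poor adherers, and people who stop the capsules without meeting a trigger, stay in if they are measured.
- **That the 4- and 8-month lipids go unused.** Statistical methods lists triglycerides among the follow-up measurements to be summarised by group. What the text does not say is that they enter the primary comparison for those who leave.
- **That losses must differ by arm.** The biochemical trigger needs high 25(OH)D and a confirmed calcium and PTH pattern, and the Safety section calls intoxication rare. The listed symptoms are non-specific, and participants and contact staff are blinded. No link between arm and new disease or drug use is stated, and no interruption rate by arm is given.
- **That the flaw is worth 6.2 to 26.2 points.** That range needs every lost participant to go one way in one arm and the opposite way in the other. It also counts ordinary departures that better retention might not recover.

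It is also fair to say that the choice of missing-data method commonly belongs to an analysis plan that is not shown, and that its absence from a condensed article is no fault.

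All of this limits the size of the point. It does not remove it, because the problem lies in rules that the article does state. An analysis plan could add imputation, but it could not recover measurements that the protocol stops taking.

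**Conclusion.** The point holds as a moderate one. The set labelled ITT is an available-case set, and the stated end of follow-up produces missing primary outcomes that this set then leaves out. Bias is possible, but its direction is undetermined and it may be small. Under the assumed one-sided losses and no true effect, it is about 1 to 3 points at 5% loss and about 2 to 7 points at 10% loss, against a planned difference of 18 points. It is zero if the lost resemble those who stay. A reader might infer that randomisation no longer protects the comparison at all. The article does not support that, because participants are analysed as randomised and the number of triggered losses is unknown.

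The conclusion rests on reading interrupted follow-up as meaning no later triglyceride measurement, which the text implies but does not spell out.

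**What to change.** 1. Reconcile the Participants, Safety and Statistical methods sections so that the end of supplementation is separate from the end of data collection. Keep stopped participants on the scheduled lipid measurements where still possible, unless they withdraw consent. No change to the clinical stopping thresholds is proposed.
2. Define ITT as all randomised participants by assigned group. Trial status gives 362 enrolled, taken here as the number randomised.
3. Include the 4- and 8-month triglycerides in the primary analysis, through a repeated-measures model or multiple imputation, and add a sensitivity analysis for missing outcomes.
4. Relabel the present set as available cases.

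**Cost.** A little more field work at workplace visits that already exist, and somewhat more analysis. Enrolment dates from November 2016 and treatment lasts 12 months, so some or all visits may already be past. The article says that the trial is not concluded, and steps 2 to 4 apply in either case. They should be settled before the code is opened.
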